## Abstract

**Background:**

Urinary incontinence occurs in 40 % of women aged 65 years and over; however, only 15 % seek care and many delay healthcare seeking for years. Incontinence is associated with depression, social isolation, reduced quality of life, falls and other comorbidities. It is accompanied by an enormous cost to the individual and society. Despite the substantial implications of urinary incontinence on social, psychological and physical well-being of older women, the impact of continence promotion on urinary symptom improvement and subsequent effects on falls, quality of life, stigma, social participation and the cost of care remains unknown.

**Methods:**

This study is a mixed methods multi-national open-label 2-arm parallel cluster randomized controlled trial aiming to recruit 1000 community-dwelling incontinent women aged 65 years and older across Quebec, Western Canada, France and United Kingdom. Participants will be recruited through community organizations. Data will be collected at 6 time points: baseline and 1 week, 3 months, 6 months, 9 months and 12 months after baseline. One of the primary objectives is to evaluate whether the continence promotion intervention improves incontinence symptoms (measured with the Patient Global Impression of Improvement questionnaire, PGI-I) at 12 months post intervention compared to the control group. Other co-primary outcomes include changes in incontinence-related stigma, fall reduction, and incremental cost-effectiveness ratio and quality-adjusted life years. Data analysis will account for correlation of outcomes (clustering) within community organizations. A qualitative sub-study will explore stigma reduction.

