### Sample size

The sample size calculations were not equivalent for all the co-primary outcomes of the study and, therefore, differ based on the various outcomes.

We hypothesize that the sample size required to demonstrate the effectiveness of the continence promotion intervention will be sufficient as it is powered to detect a minimally clinical important difference of 20 % in the proportion of participants globally rating their improvement in urinary symptoms as “much better” or “very much better,” with an expected change in the control group of 6 % [39]. As the design is a cluster randomized trial, we need to adjust for both the clustering and the effect of unequal cluster sizes [40]. Based on the results from the pilot study [26], an estimated average cluster size of 4 participants and an intra-class correlation coefficient (ICC) of 0.02, we would require a minimum of 14 community organizations per arm (a minimum of 56 participants per arm) to be able to detect a difference of 20 %, with 80 % power and alpha 0.05. To account for attrition, which we estimate to be around 15 %, we decided to set the recruitment target to at least 100 participants per arm.

The sample size needed for the falls outcome anticipates an average baseline fall rate per group of 30 % [26], and hypothesizes that the intervention will have an effect on the incidence rate of falls of 0.21 (30 % relative reduction). A minimum sample size of 388 per group (at least 97 community organizations per group) is needed to detect this minimally important difference with 80 % power, 5 % level of significance, an ICC of 0.02 and an average cluster size of 4.

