### Strengths

The strengths of this study include the robust randomized controlled trial design with baseline and long-term follow-up, the quantitative and qualitative mixed analysis and the use of multiple measures as primary outcomes. Additionally, the international platform for this study will facilitate rapid accrual of sample size and external validity at minimum cost, while meeting the needs of regulatory agencies in different jurisdictions. The synergies enabled by the intervention have the potential to produce a paradigm shift in attitudes toward incontinence in older women, and among health professionals empowered to address multimorbidity in an aging population. Although incontinence has been associated with falls, to date no trial exists that causally links reductions in falls to exposure to a continence promotion intervention that improves urinary symptoms. Furthermore, this is the first trial to assess the impact of incontinence symptom improvement, fall reduction and quality of life on QALYs and healthy active life expectancy in older women.

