### Knowledge translation

Knowledge translation is assured as our recruitment strategies reach out directly to community organizations and their constituents. The results of this study will be communicated to community stakeholders and the general public as an incontinence awareness initiative. Our ultimate goal will be to contribute to discussions around public health social policy change to support a more proactive society-wide management of incontinence. The progress of the study, interim and final results will be presented at relevant national or international conferences. Manuscripts will be submitted for publication in peer-reviewed journals. The aim is to make the intervention accessible in a train-the-trainers format to community organizations and primary care institutions after completion of the study.

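### Three tested co-primary outcomes are each sized at the full 5 % with no split or order, and I-QOL is sized on the scale but compared by subscale

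*Protocol article*

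**What the plan says.** The abstract makes improvement on the PGI-I one of the primary objectives and continues: "Other co-primary outcomes include changes in incontinence-related stigma, fall reduction, and incremental cost-effectiveness ratio and quality-adjusted life years". The Outcomes section repeats the label, calling I-QOL/stigma the second co-primary outcome and falls the third. The Strengths section counts "the use of multiple measures as primary outcomes" in the trial's favour.

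The Sample size section opens with "The sample size calculations were not equivalent for all the co-primary outcomes of the study" and gives three calculations:

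- **PGI-I:** the trial is "powered to detect a minimally clinical important difference of 20 % in the proportion of participants" who rate themselves clearly improved, "with an expected change in the control group of 6" per cent, "with 80 % power and alpha 0.05". The result is 56 participants per arm.
- **Falls:** 0.30 against 0.21, 80 % power, 5 % level. The result is 388 per group.
- **I-QOL, mapped to SF-6D:** a simulation in which a difference of 4.74 is significant at 0.05 in at least 80 % of runs. The result is 500 per group, which becomes the recruitment target.

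The Falls outcome section gives three measures (rate, proportion of women who fell, proportion of injurious falls), and the Data analysis section gives each its own model. For I-QOL, Data analysis describes a total score on a 0–100 scale and four subscales scored in the same way. The between-arm linear models, however, are specified for the subscale scores.

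**The concern.** Co-primary can mean that success on any one outcome supports a claim, or that all must succeed. The article sets neither rule. The Study hypothesis lists the expected effects together without making them a decision rule, and second and third are labels, not a testing order.

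The stated 5 % and 80 % hold for each outcome taken alone. If any win counts, the chance of at least one false claim exceeds 5 %. If all must win, the chance of success under the planned effects falls below 80 %.

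There is also multiplicity within outcomes. None of the three falls measures leads. For I-QOL, the quantity that set the trial's size, a difference on the scale, is not the one that the between-arm models are written for. As written, the plan offers four subscale comparisons and specifies no between-arm test of the sized quantity.

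**Working it through.** **Inputs.** All come from the Sample size section unless marked.
- PGI-I 6 % against 26 %; falls 0.30 against 0.21; I-QOL difference 4.74 at 500 per group.
- "an estimated average cluster size of 4 participants and an intra-class correlation coefficient (ICC) of 0.02", so the design effect is 1 + (4 − 1) × 0.02 = 1.06.
- Attrition about 15 %, so 500 × 0.85 = 425 per group.
- Assumptions: two-sided tests; I-QOL power exactly 80 % at 500 per group, since no standard deviation is given.

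**1. The plan's own figures.** For two proportions with pooled variance under the null, no continuity correction, and p̄ the mean of p₁ and p₂:

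n = [1.96√(2p̄(1−p̄)) + 0.8416√(p₁(1−p₁)+p₂(1−p₂))]² / (p₁−p₂)²

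- PGI-I: n = 52; 52 × 1.06 = 55.1, which rounds up to 14 clusters of 4 = 56. This reproduces the stated 56.
- Falls: n = 367; 367 × 1.06 = 389.0, against the stated 388. The unpooled form gives 386.1. This reproduces within rounding of method.

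Both figures are therefore two-sided 0.05 calculations with nothing held back for other outcomes.

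**2. Any win counts.** With k independent tests at 0.05 and no true effect on any of them, the error is 1 − 0.95^k.
- k = 3 (PGI-I, one I-QOL test, one falls test): 1 − 0.95³ = 14.3 %.
- k = 8 (PGI-I, four I-QOL subscales, three falls measures): 1 − 0.95⁸ = 33.7 %.
- With a common correlation of 0.5, simulation of equicorrelated normals gives about 12.5 % and 25.0 %.

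**3. All three must win.** The implied I-QOL standard deviation is 4.74 / [(1.96 + 0.8416) × √(2/500)] = 26.75. The two proportions use n/1.06.

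| Per group | PGI-I | Falls | I-QOL | Joint, independent |
|---|---|---|---|---|
| 500 | >99.9 % | 88.8 % | 80.0 % (by construction) | 71 % |
| 425 | >99.9 % | 83.4 % | 73.3 % | 61 % |

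At 500, the joint figure is 1.00 × 0.888 × 0.800 = 0.71. At 425, it is 1.00 × 0.834 × 0.733 = 0.61. With correlation 0.3 to 0.8, simulation gives 73–77 % at 500 and 64–70 % at 425. Joint power cannot exceed that of its weakest component, which is I-QOL at 80 %.

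**4. Splitting alpha instead.** At 0.05/3 the I-QOL calculation needs about 667 per group and falls about 519, against 500 planned. At 500 per group, power at 0.05/3 is about 66 % for I-QOL and 78 % for falls. A split added later would thus not fit the fixed size.

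**The case against.** The best defence is that a success rule or testing order is usually left to the statistical analysis plan, which is not shown. That stands as far as the missing rule goes: its absence from an article is not by itself an error. It does not remove what the article does fix, namely sizing at the full 0.05 for each outcome, three co-primary falls measures, and I-QOL models written for subscales when the sizing uses the scale. A later plan could impose an order at no cost in sample size, but not a split.

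The defence is also right that the eight-test count is an upper construction. Nothing says that one subscale or one falls measure would make the trial a success, and measures within a family are surely correlated.

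A reader might infer three stronger things that the article does not support.
- **The economic outcome as a fourth test.** ICER and QALY are called co-primary, but no alpha-level test is stated for them. The Economic analysis section plans a decision model, probabilistic sensitivity analysis and acceptability curves. They do not belong in the error count.
- **All-win power as the product of nominal 80 % values.** At 500 per group, falls and PGI-I have more than 80 %, so the product understates joint power.
- **An unadjusted interim look.** The Knowledge translation section says "The progress of the study, interim and final results will be presented at relevant national or international conferences". This is a dissemination statement. It plans no between-arm test and does not say that outcome data by arm would be shown, so no error inflation follows from it.

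**Conclusion.** The point holds for PGI-I, I-QOL and falls. Each is co-primary and sized at the full 5 %, with no split or order.

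- **Any-win reading:** family-wise error of about 14 % to 34 % under independence, or about 12 % to 25 % at correlation 0.5. These figures assume no true effect on any outcome.
- **All-win reading:** joint power of about 71 % at 500 per group and 61 % at 425 if independent, and 73–77 % at 500 with correlation 0.3 to 0.8. This shortfall is real but moderate. An all-win rule needs no alpha adjustment, so the two problems are alternatives and do not add up.

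The power figures depend on the I-QOL standard deviation back-calculated from exactly 80 % power at 500 per group. If the simulation gave more than 80 %, joint power rises accordingly.

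Separately from any success rule, the stated between-arm I-QOL models do not test the quantity on which the trial was sized.

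**What to change.** Before unblinding, state a fixed sequence, each step at two-sided 0.05:

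1. PGI-I rated as significant improvement (the article's top two categories) at 12 months.
2. Total I-QOL score at 12 months, with its between-arm model written out.
3. One named falls endpoint that matches the sample-size calculation.

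Step 3 needs a decision. The 388 reproduces as a comparison of two proportions, although the text calls the effect an incidence rate. If the rate is chosen, the sizing should be restated. With simple Poisson variance and one year per woman, (1.96 + 0.8416)² × (0.30 + 0.21) / 0.09² = 494, or 524 after the 1.06 design effect, which exceeds 500.

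Make the I-QOL subscales and the other two falls measures secondary. Keep ICER and QALY as estimation outside the testing family, as the Economic analysis section already plans.

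The cost is wording only. The sequence keeps 500 per group and each test at 0.05, and holds family-wise error at 5 %. With PGI-I first, its power is above 99.9 % even at 425 per group if 6 % against 26 % is true, so that gate costs almost nothing under the plan's own assumptions. The downside is that a later outcome cannot be claimed as confirmatory if an earlier one fails; falls would depend on I-QOL, whose power is about 73 % at 425. Other valid orders exist; what matters is that one is fixed before results are known.

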**Discussion:**

Community-based continence promotion programs may be a cost-effective strategy to reduce urinary incontinence, stigma and falls among older women with untreated incontinence, and simultaneously improve quality of life and healthy active life expectancy.

**Trial registration:**

ClinicalTrials.gov: NCT01858493, registered 13 May 2013

## Background

The “taboo” syndrome of urinary incontinence has traditionally been stigmatized among older women despite its remarkably high prevalence. In Canada, the United Kingdom (UK) and France, almost 40 % of women aged 65 years and older experience urinary incontinence, but little more than 15 % seek care [1–4]. For many of these women, incontinence symbolizes a decline into frailty and dependency [5]. Coping strategies include the avoidance of social activities because of the potential for embarrassment due to loss of bladder control in public, resulting in a vicious cycle of reduced participation, social isolation, depression and loss of independent living [6]. Urinary incontinence has consistently been associated with shame [6], poor quality of life [6, 7], poor self-rated health [7], social isolation [6], and depression [6, 8].

Incontinence is also linked to falls in older people, especially when leakage is associated with urgency and rushing to the toilet in order to prevent leakage [9–14]. Urge incontinence describes incontinence associated with feelings of urgency, and has been shown to increase the risk of falls by 50 % [9], with resultant fall-related injuries. The relationship between falls and urinary incontinence can be explained by shared underlying pathophysiological mechanisms, problems with dual-tasking and cortical inhibition, and white matter hyperintensities [15–17]. Urinary incontinence alone, and because of its association with falls, has been associated with functional decline, nursing home admission and significant out-of-pocket expenses [18, 19]. This is a tragedy as incontinence is largely treatable, with cures and improvements obtainable at all ages even with conservative management [20].

Receipt of care for incontinence has been shown to lead to measurable improvements in quality of life for older adults [21]. Unfortunately, almost 85 % of incontinent older women never talk to a healthcare practitioner or seek help for their condition [4, 22–24]. Women who do not seek help may consider their incontinence as not being serious enough, have inappropriate beliefs related to incontinence being a normal part of aging, or may imagine that there is nothing that can be done to treat it [24, 25].

To date, few public health initiatives have targeted continence promotion, despite its substantial social, psychological and physical ramifications for older adults. Continence promotion involves challenging inappropriate beliefs about incontinence, educating people that evidence-based therapeutic options exist, and promoting improvements and cures at all ages.

A pilot study compared the effectiveness of three experimental continence promotion interventions against a control intervention on urinary symptom improvement in 259 women aged 60 years and older with untreated incontinence [26]. Participants were recruited from community organizations [27]. The highest rate of urinary symptom improvement occurred among participants who received a combined a 1-hour constructivist learning workshop and a self-management program. Sixty-six percent of participants in this group achieved improvement in urinary symptoms, compared to 11 % of the control group (prevalence difference 55 %, 95 % confidence interval (CI) 43 –67 %, intracluster correlation 0). The number-needed-to-treat was 2 to achieve any improvement in incontinence symptoms, and 5 to attain significant improvement. Changes in knowledge and self-reported risk-reduction behaviors paralleled rates of improvement [26].

The trial described in this protocol seeks to build on the successful pilot study by testing whether the combined continence promotion intervention can diminish incontinence-related stigma and falls, and improve quality of life in addition to reducing urinary symptoms in older community-dwelling women with incontinence. This cluster randomized controlled trial, conducted internationally across the UK, France and Canada, will enable accrual of a larger sample of culturally diverse women in whom to test the continence promotion intervention. Prolonging the follow-up period to 1 year, as compared to only 3 months in the pilot project, will allow us to see if the benefits of the combined intervention can be maintained and improved over 1 year. Further, this will permit time for women to seek healthcare after they have tried some self-management tools. The impact on fall reduction, quality of life and healthy active life expectancy will also be assessed.

### Study hypothesis

We hypothesize that, compared to the control group, receipt of the combined continence promotion intervention will result in a significant improvement in incontinence symptoms in at least 20 % of women, a reduction in falls of 30 %, an expected change of 4.74 points on the Incontinence Quality of Life Scale (I-QOL) and a gain in utility points on the 6 dimensional derivative of the 12-item Short Form Health Survey (SF-6D) of 0.0126, with which to calculate cost-effectiveness, cost-utility and gains in healthy active life expectancy (Fig. 1).

**Fig. 1 Fig1:**
[figure not shown]
Logic model for the Continence Across Continents To Upend Stigma and Dependency (CACTUS-D) trial

### Aim and study objectives

This study aims to evaluate the effectiveness of a continence promotion program on incontinence symptoms, rate of falls, self-stigma and quality of life in community-dwelling women with incontinence. In addition, the study aims to evaluate the economic efficiency (incremental cost-effectiveness and cost-utility) of providing community-based group continence workshops to untreated older women with incontinence.

The objectives are to:Evaluate whether the continence promotion intervention yields significant improvement in incontinence symptoms at 1 year post intervention compared to the control group.Examine the effects of a continence promotion intervention on self-stigma among women with untreated urinary incontinence.Examine whether the receipt of a continence promotion intervention leads to a reduction in falls and fall-related injuries.Investigate the effects on quality of life and ascertain the cost-effectiveness/cost-utility of the continence promotion program for senior community-dwelling women.

## Methods/Design

### Design

The Continence Across Continents To Upend Stigma and Dependency (CACTUS-D) study is an open-label, two-arm, parallel group, multi-national cluster randomized controlled trial to be conducted across four sites. A cluster design was deemed necessary to minimize the chances of contamination between participants in different arms of the trial. Individuals in a given community often share information through discussion or direct observation. We surmised that older women rarely migrate to more than one community, hence we were confident that community-level cluster randomization would minimize the chances of contamination between the two arms of the trial.

The two arms in this trial are the continence promotion intervention arm and the sham control arm. Figure 2 shows the flow of participants through the study. A qualitative study relating to stigmatization associated with continence will be embedded in the trial with a sub-group of participants. The qualitative sub-study will be conducted across all four sites and will seek to understand the effects of a continence promotion intervention on self-stigma among women with untreated urinary incontinence.

**Fig. 2 Fig2:**
[figure not shown]
Study flow

An economic evaluation will be conducted alongside the trial to examine the difference in costs and outcomes between the continence promotion intervention and control groups. If the continence promotion intervention is deemed effective in both cost saving and improvement in outcomes, then it is labeled dominant to the comparator. An economic evaluation is useful for decision-making in comparing the cost and outcomes.

### Study participants and setting

#### Eligibility of community organizations

All community organizations in Quebec, Western Canada, France and the UK will be eligible to participate and recruit older community-dwelling women to the trial.

#### Eligibility of community-dwelling participants

Community-dwelling incontinent older women attending workshops organized by participating community organizations will be eligible to take part in the study. Women eligible for inclusion will be those aged 65 years or older who are able to communicate either in English or in French. They will have had to experience urinary incontinence with a frequency of two or more times per week, and not sought professional advice for incontinence symptoms within the past year. Exclusion criteria are women diagnosed with dementia.

### Ethical approval

The ethics review boards of the Institut Universitaire de Gériatrie de Montréal in Quebec, the University of Brunel in the UK, the University of Poitiers in France, and the University of Alberta in Alberta all approved the study protocol by 26 March 2013 (ClinicalTrials.gov identifier: NCT01858493). No personal identifiers will be used in any reports or publications. Study procedures and benefits will be explained to the enrolled women, and written consent will be obtained for baseline measurements.

### Recruitment and application of eligibility criteria

#### Organizations

Recruitment will be via community organizations. Eligible organizations will be contacted via post, telephone or Email by a research assistant, and invited to host an older women’s health workshop. Organizations will be strategically selected by convenience sampling and word of mouth to target older women. Previous organizations from the pilot study [26, 27] for this project will not be recruited. In order to be inclusive of diversity, a conscious effort will be made to approach culturally and socio-economically diverse groups of women through outreach to different community organizations in urban and rural areas from a wide area around each study site. Once the organization has consented to host a workshop and a local organizer has been selected from the organization, a mutually convenient date will be chosen for the local event. The event will be advertised via telephone calls, word of mouth, and targeted advertisements featured in online or paper newsletters, and mailed invitations, printed by the organization inviting their members to attend.

